### Sample size {14}

The mean difference of change in VISA-P score over time between the intervention and placebo group is estimated to be 13 points higher in the intervention group compared to the placebo group. The standard deviation of the difference in VISA-P score is estimated to be 19 [15]. With a power estimated to be 80% and a significance level of 0.05, the sample size calculation (performed in G*Power 3.1.9.7) led to a total sample size of 70 participants. As we will compensate for an expected loss to follow-up of 9%, 76 participants will be included in total, i.e., 38 participants per treatment arm.

### Recruitment {15}

Dutch male and female athletes (age 16–40) suffering from anterior knee pain will be informed about the JUMPFOOD study via physical therapists, sports associations, clubs, and sport physicians. Coaches and clubs within the region of the study location are also informed about the study. Additionally, local, regional, and national publicity campaigns are used to draw attention to the study. For example, the Dutch volleyball association (NeVoBo), basketball association (NBB), handball association (NHV), korfball association (KNKV), and athletics association (Atletiekunie) will be informed about this study, and athletes will be informed through their websites and newsletters.

## Assignment of interventions: allocation

### Sequence generation {16a}

Participants will be randomly assigned to either the intervention or the control group using a block randomization with blocks of 8 participants. Blocks will be based on the date of entry. The randomization list will be prepared by an independent person, not associated with the study. This person is blinded to information about the study participants. This independent person works at a different department of the Wageningen University & Research (WUR) and will only be involved in the randomization and blinding of this study. This person will not be involved in further steps or analyses of the JUMPFOOD study. Randomization of participant numbers to supplement numbers will be performed using a random number generator.

### Concealment mechanism {16b}

The allocation sequence containing the supplement numbers linked to the treatment is in a sealed “emergency code envelope.” During the entire study, the executive researcher only has a list of participant numbers and supplement numbers. The supplement number cannot be traced back to either the supplement or the placebo group.

### Implementation {16c}

The allocation list containing supplement numbers linked to participant numbers is in possession of the executive researcher, who will allocate participants to participant numbers during enrolment. The assignment to interventions is blinded and only known by the independent person who performed the randomization beforehand. The executive researcher therefore also does not know which participants are in the same group (placebo or intervention).

## Assignment of interventions: blinding

### Who will be blinded {17a}

All participants, care providers, outcome assessors, and data analysts will be kept blind to the assignment of the type of intervention. Only the independent randomization person, who is not involved in further steps or analyses of the study, knows the treatment allocation. Blinding of the hydrolyzed collagen/vitamin C supplement is possible since the placebo supplement will look, smell, and taste approximately the same. After data analysis, the codes will be broken.

### Procedure for unblinding if needed {17b}

The executive researcher will receive the code of the independent randomization person identifying which treatment the participant receives in case of an emergency in which a participant will have to be unblinded.

## Data collection and management

### Plans for assessment and collection of outcomes {18a}

Each researcher involved in this study will be trained in the study requirements; standardized measurement of height, weight, and fat percentage; how to handle the myotonometer, caliper, UTC, OptoGait, Castor, and questionnaires; how to prepare the supplements; and how to explain everything and guide the participants during study participation.

During study execution, all data that will be obtained will be filled out in Castor with additional checks within a day. On all test days, the painful knee will be marked in the morning, so every researcher knows which leg the affected leg is. Tests are first performed on the unaffected knee and thereafter on the affected knee.

For further information, see the “Outcomes {12} section.”

### Plans to promote participant retention and complete follow-up {18b}

Participants will receive their own data every test day to promote participant retention and complete follow-up. In addition, newsletters will be shared among participants showing their personal details with further explanations, and fact sheets will be shared showing the current study status and results.

### Data management {19}

Data collection will be performed using the electronic data capture system Castor. All assessors performing the measurements will be intensively trained beforehand, if not already trained by education (radiologist performing ultrasound and qualified nurses performing blood sampling). Functional tests and stiffness measurements will be performed twice or three times to promote data quality. In addition, further data quality is promoted by the use of reliable and valid measurements and questionnaires as mentioned above.

### Confidentiality {27}

Personal data of the participants that will be collected during the present study will be handled confidentially and coded, in compliance with the General Data Protection Regulation (GDPR) (Dutch: Algemene Verordening Gegevensbescherming, AVG). Included participants will be identified by an anonymous identification code which is not based on the participants’ initials, name, or date of birth. Participants will be given a unique code (10.001, 10.002, 10.003, etc.). This code is linked with the name, date of birth, and contact information of the participant in a protected file, and only the members of the research team can access this file. This study number will be used for all study documentation and all study reports or publications. Where it is necessary to be able to trace data to an individual participant, a participant identification code list can be used to link the data to the participant. Data will be stored on a secure server at ZGV for 15 years in order to be used for further analyses in line of this research. Blood samples obtained during the study will be stored for 5 years using the unique codes. The handling of personal data will comply with the GDPR. When participants give consent for participation, they also give consent for storage of their data. Study results will be published in a peer-reviewed journal.

The METC Oost-NL will be consulted when new research is carried out with the residual material taken during this current study, during the next 5 years, with the possibility of new findings about the health status of the donors.

### Plans for collection, laboratory evaluation, and storage of biological specimens for genetic or molecular analysis in this trial/future use {33}

For future analyses, we will take extra blood at baseline and 1 h after intake of the supplement, at all three test days. This blood sample will be saved for future analyses, because the results of previous measurements may give rise to follow-up measurements. For example, results for pro-collagen-1 concentrations might be a reason to subsequently test for specific amino acids or growth factors. New insights may lead to specific cytokine analysis. In addition, in an in vitro study we want to add the collected blood samples to tendon cells.

## Statistical methods

### Statistical methods for primary and secondary outcomes {20a}

Statistical analyses will be performed with SPSS software (Version 27, IBM, Armonk, NY, USA). Collected data will be checked for completeness and normality of distribution (using the Shapiro–Wilk test). For the normally distributed variables, the parametric test will be used. For the variables that are not normally distributed, the non-parametric test will be used. Normally distributed continuous variables will be presented quantitatively as mean (± SD), or graphically with mean (± SD). Data that is not normally distributed will be presented as median and interquartile range. Categorical data will be presented as percentages. A *p*-value of ≤ 0.05 will be considered statistically significant.

The primary study parameter will be the difference between intervention and placebo in the change in VISA-P score (0–100) over time. The primary outcome will first be analyzed with a linear mixed model. When the residuals of the model are not normally distributed, we will use a generalized linear mixed model instead. As independent variables, the treatment (supplement or placebo), time (time points of the measured variable) and time × treatment will be fixed factors, and the participant will be used as a random factor. Adjustments will be made for those baseline variables that are associated with the primary outcome (*p* < 0.10), using a multivariable analysis and a stepwise backward elimination strategy. Examples of potentially associated variables are baseline vitamin C and collagen amino acid intake, baseline P1NP concentrations, compliance to PTLE program, compliance to supplement use, and use of co-medication. Secondary study parameters will be reported quantitatively as well, in the most commonly used way. For the secondary study parameters, we will choose between the generalized linear mixed model and the linear mixed model in the same manner as for the primary outcome. Here, as independent variables, the treatment (supplement or placebo), time (time points of the measured variable), and time × treatment will be fixed factors, and the participant will be used as a random factor. The dependent variable is the secondary study parameter in question (with as important dependent variables/outcome measures: pain during a single leg decline squat, ultrasound imaging abnormalities, UTC findings, and tendon and muscle stiffness). The same stepwise backward elimination strategy will be used as mentioned above. For parameters that are categorical (dichotomous, nominal, or ordinal) a generalized linear mixed model will be used that is applicable for that specific secondary variable (for example a logistic mixed model for dichotomous parameters, and an ordinal mixed model for ordinal parameters). For these parameters, a similar strategy will be applied as described above.

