### Objectives {7}

The primary objective of this RCT is to evaluate whether the use of oral supplementation of hydrolyzed collagen/vitamin C in addition to usual care (education, load management advice and PTLE) is superior to usual care and placebo on Victorian Institute of Sports Assessment Patellar Tendinopathy (VISA-P) score (which rates pain, function, sports participation) after 24 weeks for athletes with PT. The secondary objective of this RCT is to evaluate whether the use of oral supplementation of hydrolyzed collagen/vitamin C in addition to usual care is superior to usual care and placebo with regard to other clinical outcome parameters, functional tests, and ultrasonographic tendon structure after 12 and 24 weeks for athletes with PT.

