### Trial design {8}

The JUMPFOOD study is a double-blinded, 2-armed randomized-controlled superiority trial (RCT). The duration of the intervention is 24 weeks after inclusion, with an additional follow-up questionnaire at 52 weeks (see Fig. 1A, B). Test days will take place at weeks 0, 12, and 24, with the first test day marking the start of the intervention period. Randomization will be performed as block randomization with a 1:1 allocation. The JUMPFOOD study will take place from February 2023 and is expected to finish at the end of 2025.

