### Outcomes {12}

#### Primary outcome measure

##### VISA-P questionnaire

The primary outcome measure of the JUMPFOOD study is the change of the validated and disease-specific VISA-P score over 24 weeks, which will be compared between the supplement and placebo groups. This is a short questionnaire specifically designed for athletes with patellar tendinopathy measuring the severity of the injury by assessing pain, function, and ability to participate in sports activities [14]. A VISA-P score of 100 indicates no pain, maximum function, and maximum ability to play sports. The score decreases with increasing severity of symptoms of PT. The VISA-P questionnaire has been translated and validated in Dutch language [14]. The responsiveness of the VISA-P scale has recently been established in athletes with patellar tendinopathy. The minimum clinically important difference (MCID) of the VISA-P score was 13 points in that study [15].

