	At home by mail or telephone	At the hospital Sports Valley	Start of study	At the hospital Sports Valley Week 0, week 12, and week 24	Online Week 6, week 18, and week 52	During the entire 24 weeks, daily	During the entire 24 weeks, weekly
Handover study information and informed consent	X						
Telephone call: discuss questions about participation	X						
Signing informed consent	X						
Online screening	X						
VISA-P	X						
Pain map	X						
Inclusion questions	X						
Hospital screening		X					
Physical examination		X					
Ultrasound		X					
Functional tests		X					
Explanation PTLE program		X					
Randomization			X				
Study measurements				X			
Body composition^b^				X			
Questionnaires^c^				X	X^a^		
Blood sampling				X			
Functional tests^d^				X			
Imaging^e^				X			
Myoton				X			
Compliance (sachets check)				X			
Supplement use						X	
PTLE program (3 times/week)^f^							X
Compliance							X

^a^Only the VISA-P is asked digitally in weeks 6, 18, and 52

^b^Consisting of length and body weight measurements and sevenfold sum of skinfolds measurements

^c^Consisting of the VISA-P, EQ-5D, MSK, CSI, SARS, OSTRC, and follow-up questions investigating satisfaction, return to sports, pain during activities of daily living, during sports and during the PTLE program, the use of co-interventions, compliance to exercise program and supplement intake, and investigating training load

^d^Consisting of the single leg decline squat and measurements of the isometric strength of the quadriceps, hamstrings, and abductors; muscle length; drop jump test; weight-bearing dorsiflexion lunge test; hoptests; and the squat vs countermovement jump

^e^Consisting of an ultrasound (grayscale and power Doppler) and UTC, with the ultrasound executed at 0 and 24 weeks and not at 12 weeks

^f^Part of usual care

Tendinopathy-related symptoms will be recorded at baseline and 6, 12, 18, 24, and 52 weeks’ follow-up (Fig. 1A) using the VISA-P score. At 6, 18, and 52 weeks, this outcome measurement will be determined using a web-based form. The follow-up questionnaire that is given at baseline and 12 and 24 weeks is also given at 52 weeks of follow-up.

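### The statistical section states the primary parameter as VISA-P change over time, without tying the test to week 24 or saying whether week 52 enters the model

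*Protocol article*

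**What the plan says.** The Protocol article describes the primary question in four places.

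- **Objectives {7}:** superiority on the VISA-P "score (which rates pain, function, sports participation) after 24 weeks for athletes with PT. The secondary objective" follows separately. The time point is week 24.
- **Outcomes {12}, VISA-P questionnaire:** the primary outcome "is the change of the validated and disease-specific VISA-P score over 24 weeks", compared between the two groups.
- **Sample size {14}:** the assumption reads "The mean difference of change in VISA-P score over time between the intervention and placebo group is estimated to be 13 points higher" on supplementation, with SD 19, 80% power and a significance level of 0.05, giving 70 participants. No week is named.
- **Statistical methods {20a}:** "The primary study parameter will be the difference between intervention and placebo in the change in VISA-P score (0–100) over time". In the linear mixed model, treatment, "time (time points of the measured variable) and time × treatment will be fixed factors, and the participant will be used as a random factor".

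The visits come from two other sections. Participant timeline {13} says: "Tendinopathy-related symptoms will be recorded at baseline and 6, 12, 18, 24, and 52 weeks". Trial design {8} says: "The duration of the intervention is 24 weeks after inclusion, with an additional follow-up questionnaire at 52 weeks".

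The statistical section therefore states a primary parameter and a model. It does not say which coefficient or contrast decides the trial, or which of the six VISA-P time points the model uses.

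**The concern.** A difference in change over time, taken from a model with a time by treatment term, reads most naturally as the joint interaction test. That test asks whether the two mean curves differ in shape anywhere. The objective asks whether the groups differ in change from baseline to week 24. The two questions can have opposite answers.

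Two errors become possible. A difference that appears early and has gone by week 24 could be reported as a positive primary result. And a true week-24 effect of the planned size could be missed, because the power of the joint test depends on the shape of the whole curve.

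If the joint test is not what is meant, at least three readings remain open: the interaction over all six time points, the interaction over weeks 0 to 24, and the week-24 contrast. The document does not choose among them, so the choice could be made after the results are seen.

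**Working it through.** **Inputs.** From Sample size {14}: difference 13, SD 19 (taken as the SD of change from baseline), alpha 0.05, power 80%, total 70, so 35 per arm. From Participant timeline {13}: VISA-P at weeks 0, 6, 12, 18, 24 and 52. Assumptions added here: a random-intercept model as in Statistical methods {20a}, equal variances, complete data, and an SD of change of 19 at every visit. The shapes of the difference curves are also assumptions, chosen to show the range.

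**Step 1. The plan's own figure.** For a two-sample t test, the noncentrality is 13 / (19 × √(2/35)) = 13 / 4.542 = 2.862 on 68 df. Two-sided power at 0.05 is 0.806. With 34 per arm it is 0.794. So 35 per arm, 70 in total, reproduces as one two-sided comparison of a single change score.

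**Step 2. Residual variance.** In a random-intercept model the variance of a change is twice the residual variance, so σ² = 19² / 2 = 180.5.

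**Step 3. Joint interaction test.** With T time points and group differences d_t, the statistic is noncentral F with T − 1 and 68(T − 1) df, and noncentrality λ = (35/2) × Σ(d_t − mean d)² / 180.5.

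**Step 4. Week-24 contrast.** This is week 24 minus baseline between groups, from the same model. Its noncentrality is 2.862 when the true difference is 13, and 0 when there is none. The df are 272 with five time points and 340 with six; power at 13 points is 0.81 either way.

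| Group differences by visit | Visits used | Σ(d − mean)² | λ | df | Joint test positive | Week-24 contrast positive |
|---|---|---|---|---|---|---|
| 0, 10, 10, 5, 0 | 0–24 | 100.0 | 9.70 | 4, 272 | 0.69 | 0.05 |
| 0, 10, 10, 5, 0, 0 | 0–52 | 120.8 | 11.72 | 5, 340 | 0.75 | 0.05 |
| 0, 13, 13, 13, 0 | 0–24 | 202.8 | 19.66 | 4, 272 | 0.96 | 0.05 |
| 0, 0, 0, 0, 0, 13 | 0–52 | 140.8 | 13.65 | 5, 340 | 0.82 | 0.05 |
| 0, 3.25, 6.5, 9.75, 13 | 0–24 | 105.6 | 10.24 | 4, 272 | 0.72 | 0.81 |
| 0, 3.25, 6.5, 9.75, 13, 6.5 | 0–52 | 105.6 | 10.24 | 5, 340 | 0.68 | 0.81 |
| 0, 3.25, 6.5, 9.75, 13, 13 | 0–52 | 140.8 | 13.65 | 5, 340 | 0.82 | 0.81 |

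The first four rows have no week-24 difference; the last three have 13 points there. A simulation of 20,000 trials for the week-52-only pattern gave 0.821 for the joint test and 0.052 for a t test on change to week 24, in agreement with the formulas.

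**Step 5. Does leaving out week 52 settle it?** No. It removes the week-52-only route, where the joint test falls to 0.05. The early-transient patterns still give 0.69 and 0.96. What matters most is that the primary test is not named.

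The loss of power is not universal. In the last row the effect is held to week 52 and the six-point joint test does as well as the contrast. The point is that its power follows the curve and not the planned week-24 difference.

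**The case against.** The strongest reply is that the document, read as a whole, already points to week 24. The outcome definition limits the primary outcome to "the change of the validated and disease-specific VISA-P score over 24 weeks", and the statistical section says it analyses the primary outcome. Week 52 is described as additional follow-up, and no objective uses it. The parenthesis on time points is generic and is repeated for the secondary outcomes. Nothing says that a joint interaction test decides the trial. A model with time by treatment can give the week-24 difference directly, and the sample size fits a single contrast. Naming the contrast may also be left to an analysis plan that is not shown.

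Most of this stands, and it limits the point. A reader might infer that week 52 is in the primary analysis. The document neither says so nor excludes it, and the outcome definition points the other way. A reader might also infer that the plan cannot test its 24-week objective. That is not supported, because the specified model can estimate the week-24 difference. The figures for a positive result without a week-24 difference hold only if the joint test is the decision rule.

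The reply does not remove the point. The statistical section is more than silent: it states the primary parameter, in words that differ from the objective and the outcome definition. An analysis plan that names week 24 would still leave the published text inconsistent. And the 24-week reading of the visits leaves the joint test open to early transient differences.

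**Conclusion.** The point holds as a gap between sections. The question is set at 24 weeks and sized as one comparison of change, but the statistical section restates it as change over time and designates no primary test. If the interaction term is used, an early difference that has gone by week 24 could give a positive result with probability of about 0.69 (10, 10 and 5 points) on weeks 0 to 24. With week 52 included, the same pattern gives 0.75, and 13 points at week 52 alone gives 0.82. A linear build-up to 13 points has power 0.72 on weeks 0 to 24, against 0.81 for the week-24 contrast.

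These sizes depend on the assumed curves, a random intercept, complete data, 35 per arm and an SD of change of 19 at every visit. They show what one permitted reading could do; they do not show that the trial will be analysed that way. The point is best treated as an improvement that costs nothing.

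**What to change.** 1. In Statistical methods {20a}, name the between-group difference in VISA-P change from baseline to week 24, estimated from the mixed model and reported in points with a 95% confidence interval, as the single primary test at two-sided 0.05.
2. State that the primary model uses visits up to week 24.
3. Report the group differences at weeks 6, 12, 18 and 52 as secondary.
4. Bring the wording on change over time in Sample size {14} and Statistical methods {20a} into line with Objectives {7} and the VISA-P outcome definition, which need no change.

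The cost is a change of wording, best made before the allocation codes are broken. No data are lost, and the sample size is unchanged, since 35 per arm already gives about 0.81 power for the named contrast.

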### Eligibility criteria {10}

In order to participate in this study, a participant must meet all of the following criteria: a clinical diagnosis of patellar tendinopathy based on a history of focal knee pain in patellar tendon or its patellar or tibial insertion in association with training and/or competition, palpation tenderness to the corresponding painful area (on the patellar tendon), and/or focal patellar tendon pain during patellar tendon loading with a pain provocation test (single leg decline squat and/or single leg jump squat, NB: imaging findings collected in this project will not be used as an eligibility criterion). Additional criteria are as follows: age 16–40 years old (the chosen age range will minimize chances of other conditions causing anterior knee pain such as osteoarthritis and osteochondrotic diseases like Sinding-Larsen-Johansson syndrome and Osgood-Schlatter disease), a current symptom duration of at least 12 weeks, sports participation at least once a week for at least 1 year before start of complaints, a VISA-P score < 80 out of 100 points, willingness to take (non-vegetarian) nutritional supplements, and willing and able to perform the PTLE program.

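### The primary model should not hinge on a residual-normality check: the switch can take the effect off the VISA-P points scale and is not needed to protect type I error

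*Protocol article*

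**What the plan says.** All references are to the protocol article.

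- Statistical methods {20a} sets the target: "The primary study parameter will be the difference between intervention and placebo in the change in VISA-P score (0–100) over time". The opening model is fixed too: "The primary outcome will first be analyzed with a linear mixed model", with treatment, time and their interaction as fixed factors and participant as random factor.
- The same section then makes that model conditional: "When the residuals of the model are not normally distributed, we will use a generalized linear mixed model instead". For VISA-P it names no distribution, link or residual type, no criterion for calling residuals non-normal, and no effect measure after the switch. The logistic and ordinal examples later in the section concern categorical parameters.
- The VISA-P questionnaire section gives the ceiling, "A VISA-P score of 100 indicates no pain, maximum function, and maximum ability to play sports", and the benchmark for relevance: "The minimum clinically important difference (MCID) of the VISA-P score was 13 points in that study".
- Eligibility {10} requires "a VISA-P score < 80 out of 100 points". The section on discontinuing or modifying interventions {11b} expects symptoms to improve in both groups because of the exercise therapy.
- Sample size {14} plans on a 13-point between-arm difference in change, SD 19, 80% power and a 0.05 significance level, giving 70 evaluable and 76 recruited.

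**The concern.** The model for the primary outcome is selected by a feature of the trial's own data. That feature depends partly on the instrument. Participants start below 80 and are expected to move towards a ceiling of 100, and scores that pile up near a bound tend to give skewed residuals. So the check can fail even when nothing is wrong with comparing the arms on mean score.

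What is at stake is the effect that gets reported. Under the linear model it is a difference in points, which can be read directly against the 13-point MCID and the 13-point planning difference. Under a generalized linear mixed model with, say, a log or logit link, it becomes a ratio or odds-type effect that cannot. Two trials with the same protocol and the same treatment benefit could then report different primary quantities, depending on a diagnostic.

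This is a stated rule, not a missing detail. A separate analysis plan could supply a family and a link. It could not retain the linear model after non-normal residuals without contradicting the sentence quoted.

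**Working it through.** **1. The plan's own figure.** Two-sided 0.05, 80% power, difference 13, SD 19. The normal approximation gives 2 × (1.960 + 0.842)² × 19² / 13² = 2 × 7.85 × 361 / 169 = 33.5, so 34 per arm. The t-test calculation gives 35 per arm (power 80.6%; 79.4% with 34), that is 70 in total as stated. Dropout: 70 / 0.91 = 76.9, against 76 stated. The trial is thus sized for a comparison of means in VISA-P points.

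**2. What a change of link does to the effect.** Suppose equal baselines, and placebo week-24 means of 70 or 80 (assumed). The same 13-point benefit becomes:

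- log link: 83/70 = 1.19, or 93/80 = 1.16;
- logit link on score/100: (0.83/0.17)/(0.70/0.30) = 4.88/2.33 = 2.09, or (0.93/0.07)/(0.80/0.20) = 13.29/4.00 = 3.32.

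One benefit in points maps to different values on the new scale, and none of them can be set beside 13 without back-transformation. These are ratios of mean scores and leave out the random effect, so they illustrate the scale and do not predict a fitted coefficient. An identity link would keep the effect in points, but the article does not require one.

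**3. How often the check might fail.** The article gives no week-24 distribution, so the following are assumptions: 35 per arm, baseline mean 56 restricted to below 80, placebo week-24 mean 70 to 85 (70 to 80 with random slopes), treatment effect 0 or 13, 3 or 5 visits, scores rounded and clipped to 0–100, 1,500 trials per setting. Shapiro–Wilk at 0.05 on the residuals stands in for the unspecified check. Conditional residuals have the estimated participant effect removed; marginal residuals do not.

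| Setting | SD of change | Conditional fails | Marginal fails | Rejection when no effect |
|---|---|---|---|---|
| Score SD 15, correlation 0.5 | 13.6–14.4 | 5.5–20.5% | 14.5–69.5% | 4.5–5.5% |
| Score SD 19, correlation 0.5 | 16.6–17.8 | 10.3–44.2% | 33.1–92.3% | 4.5–5.9% |
| Random slopes (baseline SD 13, slope SD 18, error SD 6) | 17.3–18.6 | 18–27% | 43–94% | 4.1–6.3% |
| No cap, normal (reference) | 18.8 | 4.9% | 8.8% | 5.5% |

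The capped settings run from about 6% to 94%. In the two sets whose SD of change is near the planned 19, the rates are about 10–44% (conditional) and 33–94% (marginal). The cap raises the failure rate, but whether failure exceeds 50% depends on the residual type and the week-24 level.

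**4. Is the switch needed?** The last column is a t-test on week-24 change, used as a proxy for the mixed-model contrast. It stays between 4.1% and 6.3%, with Monte Carlo standard error √(0.05 × 0.95 / 1,500) = 0.6 percentage points. A separate simulation of baseline-adjusted ANCOVA at week 24 (3,000 trials per setting, assumed 13% to 28% of participants at 100) gave 5.1% to 5.3%. Residual non-normality from the cap does not by itself disturb the type I error of the comparison of means at this size.

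**The case against.** Several points on the other side stand.

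- A reader might infer that the switch will usually happen. The document does not support that. It gives no expected week-24 scores, no share of participants at 100 and no residual type, and with conditional residuals every simulated rate is below 50%.
- A reader might also infer that a Shapiro–Wilk test governs the switch. The article ties that test to data as collected: "Collected data will be checked for completeness and normality of distribution (using the Shapiro–Wilk test". No test or threshold is given for model residuals, so the check may be graphical. The rates in the working are conditional on a stand-in.
- It would be too strong to say that a generalized linear mixed model is no remedy for a bounded score. Beta, binomial-type and ordinal mixed models are recognised options, and fitted means under any link can be turned back into a difference in points. The cap also shrinks a latent 13-point effect to about 9 to 12 points in these simulations, so modelling the bound can be worthwhile as a supplement.
- Nor can it be said that the family and link would be chosen after seeing the data, since an unseen analysis plan may name them. Blinding of data analysts until after analysis {17a} also limits steering towards the active arm, although it does not settle which effect is estimated.
- The two-stage rule itself was not simulated. No inflation, bias or loss of power from switching has been shown.

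None of this removes the core point: the article commits to replacing the model that matches its primary parameter and sample size, on a trigger that the capped score makes more likely, and with no error-rate reason to do so.

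**Conclusion.** The point holds in a limited form. The rule makes the primary model, and possibly the scale of the primary effect, depend on a residual check. Failure of that check is plausible and made more likely by the cap, but its probability cannot be derived from the document (about 6% to 94% under the assumptions listed). A non-identity link would take the effect away from VISA-P points, the scale of the primary parameter, the MCID and the planning difference; an identity link or back-transformation would not. The switch is unnecessary for type I error, which stays at about 4% to 6% with 35 per arm. That result rests on two proxies (a t-test on change and week-24 ANCOVA), not on the full mixed model.

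This concerns the interpretation and pre-specification of the main result. It does not show that the trial would reach a wrong conclusion. It should be changed, with medium confidence.

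**What to change.** For the primary outcome, delete the sentence that replaces the linear mixed model. State that the linear mixed model is the primary analysis whatever the residual check shows, and that the result is the week-24 between-arm difference in VISA-P points with its confidence interval.

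If residuals look poor, add sandwich, bootstrap or permutation inference for that same difference, or a bounded-outcome model whose family and link are named in advance. Label either as a sensitivity analysis only.

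The sample size does not change (70 evaluable, 76 recruited), because it was already planned on a difference in means. The cost is a wording change before unblinding and one additional sensitivity run.
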